**Table 10: Artemether/Lumefantrine (Coartem/Riatem) Dosing Schedule**

| **Body weight (Kg)** | **No. tablets* at 0, 8, 24, 36, 48 & 60 hrs** |
| --- | --- |
| 5 to 14.9 | 1 |
| 15 to 24.9 | 2 |
| 25 to 35 | 3 |

*Each tablet contains 20 mg of artemether and 120 mg of lumefantrine

In addition to artemether/lumefantrine, and in the unlikely event of treatment failure with that drug combination, the following regimen will also be available at the WRP KC as an alternative for the treatment of uncomplicated malaria:

- *Malarone* Pediatric Tablets (atovaquone 62.5 mg and proguanil Hcl 25 mg) dosed according to the body weight schedule presented in Table 11.

**Table 11: *Malarone* Dosage for Treatment of Acute Uncomplicated Malaria in Pediatric Patients**

| **Weight (kg)** | ***Malarone* Pediatric Tablets**: **Total Daily Dosage** | **Dosage Regimen** |
| --- | --- | --- |
| 11-20 | 250 mg/100 mg | 4 *Malarone* Pediatric Tablets as a single dose daily for 3 consecutive days |
| 21-30 | 500 mg/200 mg | 8 *Malarone* Pediatric Tablets as a single dose daily for 3 consecutive days |
| 31-40 | 750 mg/300 mg | 12 *Malarone* Pediatric Tablets as a single dose daily for 3 consecutive days |
| >40 | 1 g/400 mg | 16 *Malarone* Pediatric Tablets as a single dose daily for 3 consecutive days |

For subjects of < 11 kg body mass, the following regimen will also be available at the WRP KC as an alternative for the treatment of uncomplicated malaria:

- Quinine: Standard oral course of quinine 10 mg/kg t.i.d. for 7-10 days.

Children with manifestations of severe malaria (e.g., parasitemia > 5%, hemo-globin < 6 g/dL, coma, convulsions) will be treated with parenteral quinine, 15 mg/kg loading dose followed by 10 mg/kg, q12 hrs. Quinine will be administered in 5% dextrose. Definitive clinical management will done at the New Nyanza Provincial General Hospital (NNPGH), Kisumu, Kenya. Subjects with uncomplicated malaria and vomiting will be admitted for parenteral anti-malarials.

All study subjects treated for malaria will be followed-up (at the clinic or by field worker home visit) until resolution of symptoms. All treatment courses will be administered under supervision of the treating physician or clinical officer and recorded in the source document and in the medication section of the CRF. Subjects found to have clinical malaria will be treated before any further immunization. Subjects evaluated in this manner will be given the appropriate dose of vaccine if their clinical symptoms resolve within 3 days. If the clinical symptoms do not resolve within 3 days the subject will not be vaccinated. However, he or she will be followed for collection of safety and immunogenicity data.

During the course of evaluation for malaria, other illnesses may be uncovered in the study subjects, such as upper respiratory infections and other minor bacterial or viral infections. The pharmacy at the WRP Kombewa Clinic will provide subjects with common over-the-counter analgesics such as paracetamol as well as antibiotics for the treatment of minor ailments and infections. If further evaluation or treatment is necessary, the subject will be transferred to the NNPGH.

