## Indications for Deferral of Vaccination

**The following adverse events constitute grounds for deferral of vaccine administration at a given point in time; if any one of these adverse events occurs at the time scheduled for vaccination, the subject may be vaccinated at a later date, within the allowable time interval specified in the protocol (see Section 8.2), or may be permanently discontinued from further vaccination at the discretion of the investigator (the only withdrawals from follow-up, i.e., from the study proper, would be for withdrawal of consent). The subject must be followed until resolution of the event as with any adverse event (see Section 11). If the subject is discontinued from further vaccination, the parent(s) will be encouraged to keep the subject in the safety and immunogenicity evaluation for the duration of the study.**

- Axillary temperature > 37.5 °C or evidence of clinical malaria (see Section 8.3.1) at the time of vaccination will warrant deferral of immunization until fever and symptoms resolve.
- Any other condition that in the opinion of the investigator poses a threat to the individual if immunized or that may complicate interpretation of the safety of the vaccine following immunization.

Such subjects will be followed daily in the clinic until the symptoms resolve or the window for immunization expires. No further vaccination will be performed if the subject does not recover (axillary temperature < 37.5°C or lack of symptoms, as appropriate) within 7 days of the originally scheduled vaccination date. The subject, however, will continue to be followed for safety and immunogenicity. **If the subject meets any of the above criteria for deferral on the day of first immunization the PI may elect to exclude the subject from further participation in the study.**

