## Replacement of Unusable Vaccine Doses

In addition to study vaccines, additional single doses of FMP-1, AS02A and Energix-B® will be provided to replace broken or lost doses. All the procedures described in Section 10 still apply.

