### **Safety Cohort**

The “safety cohort” will consist of all subjects who have received at least one dose of study vaccine or comparator vaccine and for whom any data on safety are available for analysis. A subset of the safety cohort will include those who received the test article vaccine.

The presentations of safety data will explore separately the adverse experiences among subjects who received all 3 vaccinations and among those who received fewer; among those who received each of the 3 vaccine doses; and among those with clinically important violations of study protocol.

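### Sections 7.8 and 8.3.2 set different recovery limits for dosing after clinical malaria (7 days from the scheduled date; 3 days from an unstated start); separately, the replacement-dose section lists Energix-B and omits Imovax Rabies

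*Protocol*

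**What the plan says.** **Dosing after malaria.** Protocol Section 7.8 (Indications for Deferral of Vaccination) covers the case by name: "evidence of clinical malaria (see Section 8.3.1) at the time of vaccination will warrant deferral of immunization until fever and symptoms resolve". It lets the deferred child be vaccinated later, within the interval set in Section 8.2, or be stopped permanently at the investigator's discretion. It then sets an outer limit: "No further vaccination will be performed if the subject does not recover" (fever or symptoms gone, as appropriate) "within 7 days of the originally scheduled vaccination date". Table 8 in Section 8.2 gives 30 ± 7 days between consecutive doses.

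Section 8.3.2 (Management of Symptomatic Malaria during the Study) requires treatment before any further immunization and continues: "Subjects evaluated in this manner will be given the appropriate dose of vaccine if their clinical symptoms resolve within 3 days". The other branch is: "If the clinical symptoms do not resolve within 3 days the subject will not be vaccinated". It gives no starting point for the 3 days. Section 7.8 points to 8.3.1 and 8.2 but not to 8.3.2, and 8.3.2 does not point back to 7.8.

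**Replacement doses.** The section Replacement of Unusable Vaccine Doses says that "additional single doses of FMP-1, AS02A and Energix-B® will be provided to replace broken or lost doses". Sections 4.7, 7.1 and 10.1.2 name the comparator as Imovax Rabies, and it is not on that list.

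**The concern.** Both malaria rules are instructions on whether to inject a particular child, and they can give different answers. Staff who rely on 7.8 see a 7-day limit with a stated start. Staff who rely on 8.3.2 see a 3-day limit with none. Nothing says which governs, so two children with the same course of illness could be handled differently.

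The situation is foreseeable. Section 17.2.1 places the provisional vaccinations between 28 April and 21 July 2003, and Section 4.8 describes intense transmission from April through August. There are 135 × 3 = 405 planned injections.

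At stake is consistent dosing and, through it, who counts as fully vaccinated. Section 13.3.2 promises to present separately "the adverse experiences among subjects who received all 3 vaccinations and among those who received fewer", so the rule applied helps decide which side of that description a child falls on.

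The replacement-dose point is unrelated. Stocking spares from the list as written would bring in a product the trial does not use and no named spare of the comparator.

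**Working it through.** The check is a comparison of texts and a count of days. The plan states no figure to reproduce.

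**1. The two rules side by side**

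| | Section 7.8 | Section 8.3.2 |
|---|---|---|
| Applies to clinical malaria | Yes, by name | Yes, by name |
| Limit on recovery | 7 days | 3 days |
| Clock starts | Originally scheduled date | Not stated |
| If recovered in time | May be vaccinated | Will be vaccinated |
| If not recovered in time | No further vaccination | Not vaccinated |
| Refers to the other section | No | No |

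Both limits concern when the child recovers. Neither is itself a limit on the day of injection, which comes from the 30 ± 7 day window.

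**2. Where the answers differ, both clocks starting on the scheduled date (day 0)**

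- Symptoms resolve by day 3: dosing is allowed under both.
- Symptoms resolve on days 4, 5, 6 or 7: dosing is allowed under 7.8 and barred under 8.3.2. That is 7 − 3 = 4 days.
- Symptoms not resolved by day 7: dosing is barred under both.

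**3. Sensitivity to the missing start in 8.3.2**

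Suppose instead that the 3 days run from diagnosis, that malaria is diagnosed k days before the scheduled date, and that it is still present on that date. The 8.3.2 deadline for resolution is then day 3 − k, and the gap to the 7.8 deadline is 7 − (3 − k) = 4 + k days.

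| k (assumed) | 8.3.2 resolution deadline | Resolution days on which the rules differ | Gap |
|---|---|---|---|
| 0 | day 3 | 4–7 | 4 days |
| 1 | day 2 | 3–7 | 5 days |
| 2 | day 1 | 2–7 | 6 days |
| 3 | day 0 | 1–7 | 7 days |

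The values of k are illustrative; the protocol gives no distribution of diagnosis times.

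**4. Scale**

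Each cohort has 30 FMP-1 and 15 comparator children (Section 7.2). One child who misses a dose because of the rule applied is 1/30 = 3.3% of an FMP-1 group or 1/15 = 6.7% of a comparator group. The protocol gives no rate of clinical malaria on dosing days. The 83% figure in Section 4.8 is parasite prevalence and cannot stand in for one, so the number of affected children cannot be estimated.

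**5. Replacement doses**

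Section 10.1 describes two study vaccines, FMP-1 (with AS02A) and Imovax Rabies. The replacement list has FMP-1, AS02A and Energix-B. The comparator needs 45 × 3 = 135 planned doses, and Sections 10.2.3 and 10.6 allow only one dose per vial, so a broken Imovax vial cannot be covered from another vial already in use.

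**The case against.** The strongest defence is that the two malaria texts can both be obeyed. Section 7.8 is permissive, covers any fever, malaria or investigator concern, and can be read as an outer limit; 8.3.2 is the malaria section and sets a tighter one. Withholding after day 3 breaks neither. For a first dose, 7.8 also lets the PI exclude a child who meets a deferral criterion, so the practical question is mainly about doses 2 and 3. All of this stands. It does not remove the problem, because 7.8 also addresses malaria by name and sends the reader to 8.3.1 and 8.2 but not to 8.3.2. Someone who doses a child recovered on day 5 complies with the section they were reading and, if the 3 days run from the scheduled date or earlier, breaches the other.

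Four stronger readings are tempting and not supported:

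- That neither limit has a clock start. Section 7.8 does state one; only the 3 days in 8.3.2 lack it.
- That 8.3.2 fixes a last day for dosing. It limits when symptoms must resolve. A child diagnosed 3 days early whose symptoms clear by day 0 is not barred from a dose on day 1 or 2.
- That the inconsistency biases the comparison of arms. Both rules apply alike to both vaccines in a blinded trial, and an affected child remains in the safety and immunogenicity cohorts. Section 13.3.2 promises a descriptive presentation; the percentages above are only a scale and are not a statistic the plan defines.
- That a child might be given Energix-B, or that Imovax will run short. The comparator is identified throughout, the replacement section itself keeps all Section 10 procedures in force, and 135 is the planned dose count. It is not evidence of a shortage.

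**Conclusion.** The point holds as two separate, minor operational corrections.

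(1) Sections 7.8 and 8.3.2 give different recovery limits for the same child and are not linked. With both clocks on the scheduled date, they disagree for symptoms resolving on days 4 to 7. If the 3 days run from a diagnosis 1 to 3 days earlier, the gap between the resolution deadlines widens to 5 to 7 days. The day ranges rest on those assumed starts, because 8.3.2 names none. The consequence is possible inconsistent dosing and some noise in the descriptive split between three doses and fewer. No endpoint definition, test or sample size is affected.

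(2) The replacement list names a product that is not a study vaccine and omits the comparator. The consequence is limited to whether the right spare is on the shelf.

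Confidence in both textual findings is high. How often either would matter cannot be judged from the protocol.

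**What to change.** **Malaria deferral.** Put one symptom-resolution limit with one explicit start in both sections, and have each refer to the other. The default should be the stricter 3 days. Suggested text: *After clinical malaria, a dose may be given only if symptoms have resolved within 3 days of [start to be chosen], and doses 2 and 3 must still fall within 30 ± 7 days of the preceding dose.*

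The clinical team should choose the start: diagnosis or start of treatment, or the originally scheduled date. This is a clinical choice and more than a wording change. The sentence in 8.3.2 follows those on evaluation and treatment, so a start at diagnosis is a natural reading. Counting from the scheduled date would loosen that reading for a child diagnosed k days earlier, moving the deadline from day 3 − k to day 3. The 7-day limit in 7.8 can stay for the other grounds for deferral.

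**Replacement doses.** In Replacement of Unusable Vaccine Doses, replace Energix-B with Imovax Rabies, and check the vaccine order against the corrected list.

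The cost is short text corrections, one decision by the clinical team and a check of the order, all before first dose. No analysis or sample size changes.

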# SAMPLE HANDLING & ANALYSIS

## Overview of Collection Time Points

Blood will be collected from study subjects by venipuncture up to 11 times during the study. The maximum amount of blood requested from any subject for standard collection during the study should not exceed 22 ml. However, additional blood may be obtained as deemed necessary by one of the investigators or clinicians to evaluate any illness or condition.

***Safety***

Tests for CBC, creatinine, ALT, at screening, and approximately at Study days 0, 14, 30, 44, 60, 74, 90, and Hbg every 3 months thereafter will be performed at the WRP Kombewa Clinic.

***Serology***

Separation of serum/plasma from the venous blood will be performed at the WRP Kombewa Clinic and serum samples (approximately 0.5-1.0 ml) will be aliquoted for later use to determine anti-MSP-1 antibody levels at approximately Study days 0, 14, 30, 44, 60, 74, 90 and every 3 months thereafter until the conclusion of the study.

## Handling of Biological Samples Collected by the Investigator

### Instructions for Handling of Serum Samples

1. Collection

Venous whole blood will be collected observing appropriate aseptic conditions. Serum will be collected whenever possible using VacutainerÒ tubes with integrated serum separator (e.g. Becton-Dickinson VacutainerÒ SST or CorvacÒ Sherwood Medical) or serum microtainers so as to minimize the risk of hemolysis and to avoid blood cell contamination of the serum when transferring to standard serum tubes. Serum samples will be collected from EDTA or heparinized blood following centrifugation at 2000 g for 3 min.

2. Serum separation

These guidelines aim to ensure high quality serum by minimizing the risk of hemolysis, blood cell contamination of the serum or serum adverse cell toxicity at testing.

- For separation of serum using Vacutainer® tubes, the instructions provided by the manufacturer should be followed.
- Following separation, the serum should be transferred to the appropriate standard tubes using a disposable pipette. The serum should be transferred as gently as possible to avoid blood cell contamination.

• The tube should not be overfilled (max. 3/4 of the total volume) to allow room for expansion upon freezing.

• The tube should be identified by an appropriate cryo-resistant label.

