***Serology (Antibody Responses)***

Serological assays will be performed at the USAMRU-Kenya, for antibody determination. Serum will be collected at indicated time points (see Section 9.1). Blood for analysis of antibody responses will be obtained from each subject and allowed to clot for one hour at room temperature, and serum will be separated and frozen at  -50oC until tested. All blood samples will be labeled with the KEMRI SSC number, WRAIR protocol number, the SID number and the date the sample was obtained (See Section 9.2.2 ).

Immunogenicity (antibody levels) will be determined by evaluating antibody (IgG) responses to the *P. falciparum* MSP-142 as measured using standard ELISA methodologies with appropriate capture antigens.

*Optional Immunological Readouts*

Results from these optional tests will not be encoded into the final database but will be analyzed and summarized separately by WRP or WRAIR. Immunofluorescence (IFA) titers against whole merozoites may also be measured in subjects both pre- and post-immunization; standard procedures will be followed. A subject will be considered a seroconverter by IFA if, two weeks after the second dose of vaccine, the subject develops an antibody titer (as measured by the highest IFA titer that gives a positive reaction) that is greater than 4 times that of the pre-immune serum. IFA assessments will be performed in either the Department of Immunology, WRAIR or at WRP Kisian.

Any serum not immediately used in antibody assays will be stored indefinitely at  -50°C and may be used in additional *in vitro* tests which may be useful in optimizing the follow-up of study subjects or in evaluating the immune response to the test vaccine preparation in these subjects. If this assay is not specified in this protocol, approval will be requested from the pertinent IRB(s) should the need for that assay arise.

*Other Studies*

Long-term storage of sera will be undertaken so that other laboratory assays or tests, unanticipated at the present time, may be done in the future. Any such proposal for future testing, however, must be submitted for approval to the KEMRI ERC.

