## Secondary Endpoints

Anti-MSP-1 antibody titers at timepoints at which blood samples are taken for serology.

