### Analysis of Immunogenicity

For each dose group and age group, and at each time point, anti-MSP-1 antibody levels will be presented as geometric means of OD units with 95% confidence interval tabulated. The time course of antibody levels will be described through longitudinal models.

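### Section 9.2.1 takes antibody serum from EDTA or heparinised blood, which yields plasma, while Section 9.3 requires clotted blood: the only secondary endpoint can be measured in two specimen types that the label does not tell apart

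*Protocol*

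**What the plan says.** Three places in the protocol describe how the antibody specimen is obtained.

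- Section 9.2.1 (Instructions for Handling of Serum Samples) opens with "Serum will be collected whenever possible using" serum-separator tubes or serum microtainers. It then says, without any condition: "Serum samples will be collected from EDTA or heparinized blood following centrifugation at 2000 g for 3 min".
- Section 9.3, in the paragraph Serology (Antibody Responses), says that blood for antibody analysis is to be "allowed to clot for one hour at room temperature, and serum will be separated and frozen at" the stated storage temperature.
- Section 9.1 (Serology) says: "Separation of serum/plasma from the venous blood will be performed at the WRP Kombewa Clinic". The same sentence goes on to speak of serum aliquots for "anti-MSP-1 antibody levels at approximately Study days 0, 14, 30, 44, 60, 74, 90 and every 3 months thereafter".

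The endpoint in Section 13.2 is "Anti-MSP-1 antibody titers at timepoints at which blood samples are taken for serology". Section 13.5.2 plans the following: "For each dose group and age group, and at each time point, anti-MSP-1 antibody levels will be presented as geometric means of OD units". Each mean is to carry a 95% confidence interval. On change over time, that section adds: "The time course of antibody levels will be described through longitudinal models".

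Section 9.2.2 lists the label contents: a barcode, the two study numbers, the subject number and the collection date. Specimen type is not on that list.

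**The concern.** EDTA and heparin stop blood from clotting. Spinning such blood for three minutes gives plasma, and it cannot meet the one-hour clotting step in Section 9.3. The two instructions are therefore incompatible for the same assay, and Section 9.1 does not choose between them.

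The titre is a dilution-based reading, to be summarised by dose group and age group at every visit and modelled over time. If some aliquots are plasma and others serum, part of the variation between visits or dose cohorts could come from the specimen and not from the vaccine. With no specimen type on the label, an analyst could not separate the two later. At stake is the clarity of the immunogenicity description. The primary safety endpoints are not at stake.

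**Working it through.** The protocol states no figure on this point, so there is none to reproduce. The check is first a comparison of the texts, then a count of the samples exposed, then an illustration under stated assumptions.

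**1. Texts side by side**

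- Section 9.2.1, first instruction: serum-separator tube or serum microtainer, when possible. Product: serum.
- Section 9.2.1, second instruction: EDTA or heparin tube, 3-minute spin. Product: plasma, although the text calls it serum.
- Section 9.3: clot for one hour, then separate. Product: serum.
- Section 9.1: separation of serum/plasma, then serum aliquots. Product: left open at the separation step.

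The second instruction sits under a heading about serum samples and names serum samples. Nothing limits it to the tube for the complete blood count (CBC). If it is read as a fallback for when separator tubes cannot be used, it permits two matrices outright.

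**2. Samples exposed**

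Section 9.1 gives seven scheduled days (0, 14, 30, 44, 60, 74, 90). Section 8.2 adds three quarterly visits (Visits 21 to 23).

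7 + 3 = 10 samples per child; 135 × 10 = 1,350 samples at most.

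**3. How far a mixture could move a result**

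Let f be the ratio of a plasma titre to a serum titre, and q the difference between two groups or visits in the share of samples that are plasma. The ratio of geometric means is then multiplied by f^q. The documents give neither quantity. The ranges below are assumptions.

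| f (assumed) | q = 0.25 | q = 0.50 | q = 1.00 |
|---|---|---|---|
| 0.80 | 0.946 | 0.894 | 0.800 |
| 0.90 | 0.974 | 0.949 | 0.900 |
| 0.95 | 0.987 | 0.975 | 0.950 |

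**4. Yardsticks from Table 1 (Section 4.5.1, Clinical Trials; Day 98; five adults per arm)**

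- 25 versus 50 µg: 53569 / 42799 = 1.25.
- 25 versus 10 µg: 53569 / 26626 = 2.01.
- Rise from Day 0 at 50 µg: 42799 / 22 = about 1,945-fold.
- Log-scale SD = sqrt(2 × ln(mean / geometric mean)). 10 µg: sqrt(2 × ln(32648 / 26626)) = 0.639. 25 µg: sqrt(2 × ln(57771 / 53569)) = 0.389. 50 µg: sqrt(2 × ln(50053 / 42799)) = 0.560.
- 95% confidence factor for the geometric mean of a dose group of 30 = exp(1.96 × SD / sqrt(30)), which runs from 1.15 (SD 0.389) to 1.26 (SD 0.639).

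**5. Reading the two together**

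Only the extreme cell (f = 0.80, q = 1, where one group or visit is all plasma and the other all serum) gives a factor of 0.80, or 1/0.80 = 1.25 the other way. That would cancel a dose ratio of 1.25 (1.25 × 0.80 = 1.00). The next largest shift is 0.894 (1/0.894 = 1.12), which is smaller than the narrowest confidence factor of 1.15. A mixture with q = 0.25 moves a ratio by about 1% to 5%. Even the extreme cell leaves 1,945 × 0.80 = 1,556-fold of the adult rise. To mask a response altogether, that cell would need a true rise of no more than about 1.25-fold.

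**The case against.** The best defence is that the assay-specific text is clear. Section 9.3 governs blood for antibody analysis and requires clotting. The visit lists in Section 8.2 ask for serum, and Section 9.2.1 itself puts separator tubes first. In Section 9.1 the word plasma belongs to the separation step, and the same sentence speaks of serum aliquots. Section 9.3 also refers to detailed laboratory procedures that are not shown and may settle practice. Only a secondary endpoint is touched, and Section 13.5.2 plans no between-group test on it. Blinding and randomisation within each cohort make a difference between FMP-1 and rabies recipients unlikely.

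Most of this stands. It shows that the likely intent is clotted serum, and it limits the weight of the point. It does not remove the sentence in Section 9.2.1, which is unconditional and conflicts with Section 9.3.

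A reader might go further and infer that staff short of blood would turn to the anticoagulated tube, that this would happen most in the youngest children, and that titres would therefore be biased by age. The documents do not support that. One 2 ml draw does serve both the safety tests and serology, but no passage ties the EDTA/heparin sentence to volume, and none reports short draws by age. Nor does any passage give a dilution percentage or mention a liquid anticoagulant, so no particular bias can be claimed. The documents also do not show that two matrices will in fact be used, only that the text allows it.

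**Conclusion.** The contradiction is real and should be corrected, as a minor point. Section 9.2.1 gives a wrong instruction for serum. It conflicts with Section 9.3, and the label would not reveal which instruction was followed. The effect is confined to the anti-MSP-1 titre.

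Its size cannot be taken from the documents. Under the assumed ratios of 0.80 to 0.95, an imbalance of a quarter to a half in plasma share would shift a ratio of geometric means by about 1% to 11%. That is avoidable noise in a small dose contrast or a modest decline over time, and it is not enough to hide the main vaccine response. The yardsticks come from five adults per arm in an earlier study on a different schedule. Malaria-exposed children may start from higher titres and vary more, so these figures serve for scale only. Mixing across visits, or between dose cohorts that start two weeks apart, is more plausible than a difference between vaccine arms within a cohort.

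**What to change.** - In Section 9.2.1, delete the EDTA/heparin sentence, or state that it applies only to the CBC sample.
- In Section 9.1, replace serum/plasma with serum.
- State that every anti-MSP-1 sample is clotted serum, prepared as in Section 9.3.
- Record the specimen type of any exception on the sample log, so that a sensitivity analysis can be run.

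Two further steps should not be taken. Plasma results should stay in the main analysis, because Section 13.3.3 admits all subjects with assay results and an exclusion would narrow that cohort for an effect of unknown size. No tube-filling order should put serology ahead of the safety laboratory tests taken from the same 2 ml, because safety is the primary objective and laboratory toxicities feed the dose-limiting criteria in Section 7.9.2.

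The cost is a short text correction and one extra field on the sample log. It should be made before the first sample is drawn, because the listed label contents would not allow the specimen type to be recovered afterwards.
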